**Table 2- T2:**
[figure not shown]
OHIP-14 main domain.

In this paper we will evaluate Ohip-14 by the additive method and domain evaluation. In the additive method, when the value is greater than 1, the negative impact on the individual's life can be considered. Ohip-14 will be evaluated at baseline and after 3 months for all individuals by an auxiliary.

*Collection and analysis of cytokine profile of crevicular gingival fluid* - Firstly, the biofilm present will be cured in the supra-gingival portion to avoid sample contamination. The site will be insulated with cotton rollers. A sterilized paper cone (#25 – Allprime cellpack, Brazil) will be inserted into the biological space of the vertical molar at 2 points: in the center of the buccal and lingual teeth until resistance is felt. The cone will be in position for 30 seconds. If there is contamination with blood should use new cone after 90 seconds. 10 cones should be collected, 1 for each cytokine, at the 2 analysis points. The cones will be placed in 1 sterile 1.5 ml micro centrifuge tube (Eppendorf, Sigma, CA, USA) and stored at −80° C.^[39]^ We will make another spare tube with 5 more cones in the same way as described. During collection will be stored on ice inside a properly identified Styrofoam. The collected samples will be stored at −80°C until further analysis and will be collected by an auxiliary.

*Determination of crevicular gingival fluid levels of the inflammatory markers* - TNF-α, IL1-β, IL-6, IL-8, and IL-10 will be performed by ELISA using commercial kits (Peprotech Inc., Rocky Hill, NJ, USA), according to manufacturer's instructions. This collection will be performed in the same periods of PBM application: before the placement of the mini-implant, immediately (T0), 3 (T1) and 7 (T2) days after, and at T1 of the 30th and 60th day.

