*Analysis of oral health-related quality of life (Oral health impact profile questionnaire - Ohip-14)* - This questionnaire is a simplified form of the original OHIP-49 questionnaire. Ohip-14 will be used to assess the impact of oral health on the quality of life of research participants.^[49]^ Ohip-14 is used to measure perceived needs. It measures the impact of oral changes on oral health related quality of life. The participant will answer 14 questions by giving their answers the values 0 (never), 1 (almost never), 2 (sometimes), 3 (most of the time) and 4 (always).

It can be analyzed from 2 perspectives:

Additive method - Points are summed (0–56), with 56 being the biggest impact on quality of life.Domain Assessment - OHIP-14 has a total of 7 domains, which can also be scored from 0–4, with 4 being the biggest impact. To arrive at the result, the 2 questions of each domain are summed and divided by 2. Domain 1 refers to functional limitation, domain 2 refers to physical pain, domain 3 refers to physical limitation, domain 4 refers to psychological discomfort, domain 5 refers to psychological disability, domain 6 refers to social discomfort domain 7 refers to general disability (Table 2).

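### The OHIP-14 cut-off for negative impact (>1) sits at the floor of the 0–56 total it is attached to, so it is uninformative as a descriptive label

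*Protocol article*

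**What the plan says.** Section 2.13 (Study variables) lists OHIP-14 as a secondary variable, measured at baseline and 90 days. Its scoring is fully specified:

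- **Items:** "The participant will answer 14 questions by giving their answers the values 0 (never), 1 (almost never), 2 (sometimes", and so on up to 4 for *always*.
- **Additive total:** "Points are summed (0–56), with 56 being the biggest impact on quality of life".
- **Domains:** "OHIP-14 has a total of 7 domains, which can also be scored from 0–4, with 4 being the biggest impact"; to obtain each one, "the 2 questions of each domain are summed and divided by 2".

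The text below Table 2 says that this trial will use both scores, and then gives the threshold: "In the additive method, when the value is greater than 1, the negative impact" on the person's life may be inferred.

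Section 2.14 (Statistical analysis) plans a two-way ANOVA with Bonferroni tests for all measurements. It names no analysis of the proportion of patients above a cut-off.

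**The concern.** The threshold is expressly attached to the 0–56 total, where a value of 1 is one step above the minimum. A label of negative impact that begins at a total of 2 puts a patient with almost no complaints in the same class as one at the maximum. This is a rule the article states on a scale the article defines, so it is not a detail left to a fuller document.

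What is at stake is how the quality-of-life result is described. If the percentage of patients negatively affected is reported by arm and visit under this rule, it would hide large changes in individual patients and could be read as a clinically meaningful rate, which it is not.

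**Working it through.** **Inputs from section 2.13.** 14 items scored 0 to 4; total = sum of the items; domain score = (item a + item b)/2; negative impact if total > 1.

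**Step 1: reproduce the stated ranges.** Minimum total 14 × 0 = 0 and maximum 14 × 4 = 56. Maximum domain score (4 + 4)/2 = 4. Both agree with the article.

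**Step 2: locate the cut-off.**
- Totals without the label: 0 and 1. Totals with it: 2 to 56, which is 55 of the 57 possible values.
- The cut-off is at 1/56 = 1.8% of the scale, and the lowest labelled total at 2/56 = 3.6%.
- A total of 2 arises from two *almost never* and twelve *never* answers, or from one *sometimes* and thirteen *never*. The mean item score is then 2/14 = 0.14 out of 4.
- *Almost never* to every question gives 14 × 1 = 14, far above the cut-off.

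**Step 3: what change it registers.** A fall from 20 to 5 keeps the label, since 5 > 1. A patient starting at 20 would have to reach 1, a fall of 19 points, before the class changed.

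**Step 4: share of patients labelled.** The article gives no OHIP-14 mean, SD or item frequencies, so every figure in steps 4 and 5 rests on assumed distributions. The table takes the total as Poisson, or as negative binomial with dispersion k from 0.5 to 4, ignoring the upper limit of 56:

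| Assumed mean total | P(total > 1) |
|---|---|
| 2 | 37% to 59% |
| 5 | 56% to 96% |
| 10 | 68% to 100% |
| 15 | 73% to 100% |

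For example, Poisson with mean 2 gives 1 − e^(−2)(1 + 2) = 0.594.

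A second model takes independent items, each with chance p of a non-zero answer, half of these being *almost never*: P(total > 1) = 1 − (1−p)^14 − 14(p/2)(1−p)^13. This gives 59%, 88% and 97% for p = 0.1, 0.2 and 0.3.

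**Step 5: information lost if arms were compared on the label.** This comparison is not planned; it only shows the size of the loss. With 17 per arm (section 2.10), two-sided alpha of 0.05, assumed mean total 10 against 5 and k = 2:
- Label: P(total > 1) is 0.926 against 0.802, with power of about 18%.
- Total: variance = mean + mean²/k, so 10 + 50 = 60 and 5 + 12.5 = 17.5. SD = √[(60 + 17.5)/2] = 6.22, the difference is 5, and power is about 65%.

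Across assumed means of 2 to 15, reductions of 30% or 50%, and k of 1 or 2, power is 6% to 30% for the label and 13% to 68% for the total.

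**The case against.** The best defence is that nothing in the plan depends on this sentence. It is worded permissively and reads as an aid to interpretation. No section makes the dichotomy an endpoint or a responder definition, and section 2.14 compares measurements by ANOVA, a method for scores and not for a yes/no class. This stands, and it confines the point to description.

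Three stronger readings are tempting, and the documents support none of them:

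- *Nearly every patient would be labelled.* That is plausible for adults who have lost a lower first molar, but the article supplies no distribution. At an assumed mean total of 2 the share is 37% to 59%. The independent-item model probably overstates it as well: answers on one questionnaire tend to correlate positively, which at the same item frequencies puts more patients at 0 or 1.
- *OHIP-14 could not show a change or an arm difference.* Even the label has low power and not zero power, and part of that weakness comes from the sample size, since the total itself reaches only 13% to 68% in the same cases. The planned analysis of the scores does not pass through the label.
- *The threshold was meant for the 0–4 domain scores.* There, >1 would mean an average above *almost never*, a more natural cut at 1/4 = 25% of the scale. The article does not say that this was intended.

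It can also be said that >1 on the total is a crude flag for any impact at all. That is coherent, but the article calls it negative impact on the person's life, and the flag carries little information.

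**Conclusion.** The point holds as a minor flaw in the description of a secondary variable. By the article's own scoring, the rule separates totals of 0 and 1 from totals of 2 to 56 and is blind to any change within the latter range. That conclusion needs no assumption.

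The proportion of patients labelled does depend on assumptions: roughly 37% to nearly 100% for assumed mean totals of 2 to 15. The OHIP-14 comparison between arms is not invalidated, because the planned ANOVA uses the scores. The primary variable is unaffected.

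**What to change.** In section 2.13, remove the >1 rule from the additive score and say that the total and the seven domain scores are reported as continuous. Compare the day-90 total between arms adjusted for the baseline total, which is already collected. Analysing scores is in line with what section 2.14 plans; the baseline adjustment is an addition to it.

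If a cut-off is kept for description, state which scale it belongs to and justify it. It should not simply be moved to the domain scores, because the article gives no basis for that.

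The cost is one changed sentence and slightly different analysis code. No new data, visits or patients are needed.

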### Statistical analysis

2.14

Statistical analysis will be performed using only data obtained from patients who complete the study. The Kolmogorov-Smirnov test will be applied prior to data analysis to assess the normality of each parameter. Bidirectional analysis of variance (ANOVA) followed by Bonferroni test will be used to compare all measurements. All tests will be performed using Graphpad Prism 5 (GraphPad Software, San Diego, USA). The significance level will be set at p < 0.05.

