### Inclusion/exclusion criteria

2.4

Patients who are latex allergic, pregnant or breastfeeding, smokers, diabetics, patients undergoing head and neck radiotherapy, coagulation disorders requiring antibiotic prophylaxis for placement of mini-implants, with absolute indication for use of local anesthetics with vasoconstrictors, with decompensate systemic disease, with systemic or local infection (periodontitis or periodontal abscess), who have used anti-inflammatory drugs in the last 3 months before orthodontic treatment, will be excluded from the search.

Healthy patients (ASA I - negative medical history), systolic blood pressure less than 140 mm Hg and diastolic blood pressure less than 90 mm Hg, heart rate with 70 ± 20 beats/minute, requiring oral rehabilitation after loss of some posterior lower dental element (1st molar), with favorable periodontal condition to the installation of mini-implants and who agree and sign the informed consent, will be included.

Patients who may have any complications during the research period, such as: allergic reactions to any of the materials used, allergic reaction to paracetamol, have taken any other drug than the one available, etc. Or those who are in any way unable to attend any of the appointments on the scheduled dates (in all, will be 10 dates, within 3 months), change cities, or simply no longer wish to participate in the survey, will be automatically excluded, without any compromise or damage to it (with removal of the installed apparatus). They will still be advised not to go to other professionals to intervene or continue treatment. Patients will be assisted by researchers for all research problems.

Any questions during the research period should be informed to the researcher so that the researcher can take the appropriate measures (the latter should provide some form of personal contact).

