### Randomization

2.5

To randomly assign participants to the experimental groups, a 40-number draw (34 patients + 20% of drop out, if need be) will be conducted using the Microsoft Excel 2017 version program. The distribution of the groups will be identical (1: 1) for both groups. Distribution will be performed in a blocked manner (5 groups of 8 patients). Opaque envelopes will be identified with sequential numbers (1 to 40) and inside there will be information from the corresponding experimental group according to the order obtained in the draw. The envelopes will be sealed and remain sealed in numerical order until the time of mini-implant placement and laser application. The draw and preparation of the envelopes will be performed by a person not involved in the study. Immediately before the laser application, the treating researcher will open 1 envelope (without changing the number sequence) and perform the indicated procedure. Three additional patients will be included in each group due to the drop out predicted in every clinical study (considering a 20% drop out). The author of the research will be responsible for the storage (digital platforms) and tabulation of information, being the statistician responsible for analyzing the data obtained at the end of the research. These same envelopes will contain the patient records (with anamnesis sheet, ICF and radiographs) and will be kept on file.

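### Completer-only analysis combined with automatic exclusion after randomisation can bias the comparison, most clearly for pain and analgesic use

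*Protocol article*

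**What the plan says.** The analysis set is fixed in section 2.14 of the protocol article: "Statistical analysis will be performed using only data obtained from patients who complete the study". The sentence covers every outcome.

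Section 2.4 (Inclusion/exclusion criteria) lists the ways in which a patient fails to complete:

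- "Patients who may have any complications during the research period", with allergic reactions given as examples;
- patients who "have taken any other drug than the one available, etc";
- "those who are in any way unable to attend any of the appointments on the scheduled dates", with 10 dates over 3 months;
- patients who move city or withdraw.

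All of these "will be automatically excluded, without any compromise or damage to it (with removal of the installed apparatus").

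Section 2.5 (Randomization) fixes the time of allocation: "The envelopes will be sealed and remain sealed in numerical order until the time of mini-implant placement and laser application". Section 2.10 (Experimental design) likewise has the envelope opened just before the laser is applied. Section 2.1 allows 3 extra patients per group if there is dropout. No section of the article provides an analysis of all randomised patients or follow-up of those excluded.

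**The concern.** Randomisation balances the arms at the moment the envelope is opened. A rule that then removes patients because of what happens during follow-up keeps that balance only if the removals have nothing to do with the outcome, or act in the same way in both arms.

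The drug rule is the plainest problem. VAS pain and analgesic count are secondary outcomes (section 2.13), and the laser is meant to act on pain (section 2.12). A patient whose pain is not controlled by the supplied paracetamol is a likely one to take something else, and is then dropped together with all VAS, analgesic and cytokine data already collected. If the laser relieves pain as hypothesised, this happens more often in the sham arm.

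The complication rule could reach the primary outcome. The Discussion notes that a mini-implant can be displaced, or lose stability when the tissue around it is inflamed, and either could affect tooth movement.

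With 34 to 40 patients, a handful of selective losses carries weight.

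**Working it through.** **1. Are the exclusions after randomisation?** Section 2.12 applies the laser on days 0, 3 and 7 of each of three cycles starting at days 0, 30 and 60, and ends at day 90. The dates are therefore 0, 3, 7, 30, 33, 37, 60, 63, 67 and 90, which matches the 10 in section 2.4. The envelope is opened on day 0, so 9 dates lie after randomisation. Drug use, missed dates and complications during follow-up all come after allocation.

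**2. Effect of the drug rule on the pain comparison.** The article gives no rate of other drug use, so the inputs are assumptions: pain is normal with SD 1, the sham mean is 0, the PBM mean is −0.5, and every patient above a common cut-off c takes another drug and is removed. The mean of those kept is

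- sham: −φ(c)/Φ(c)
- PBM: −0.5 − φ(c + 0.5)/Φ(c + 0.5)

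| Sham removed | c | PBM removed | Sham mean kept | PBM mean kept | Observed benefit | Share of 0.5 |
|---|---|---|---|---|---|---|
| 10% | 1.282 | 3.7% | −0.195 | −0.585 | 0.390 SD | 78% |
| 20% | 0.842 | 9.0% | −0.350 | −0.678 | 0.328 SD | 66% |
| 30% | 0.524 | 15.3% | −0.497 | −0.779 | 0.282 SD | 56% |

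Under this mechanism the bias runs towards no effect: the rule hides part of a real pain benefit.

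**3. Reach of the attendance rule.** I read section 2.4 to mean that a single missed date is enough. With an assumed independent miss rate q on each of 9 dates, the share excluded is 1 − (1 − q)^9:

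- q = 2%: 1 − 0.98^9 = 16.6%
- q = 5%: 1 − 0.95^9 = 37.0%

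Of the 40 patients that section 2.5 allows for, that is 40 × 0.166 = 6.6 or 40 × 0.370 = 14.8. The 6 extra patients cover a loss of 6/40 = 15%, which is reached at q = 1 − 0.85^(1/9) = 1.8% per date. The Discussion calls dropout unlikely because the implant is in place, but that argument does not cover exclusion by rule.

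**4. The primary outcome.** Sections 2.10 and 2.13 measure the angle only at baseline and at day 90. A patient excluded earlier has no follow-up angle. The documents give neither a loss rate by arm nor a relation between complications and angle, so no bias can be computed.

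**The case against.** Several points on the other side stand.

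- **Bias is not certain.** Equal losses by the same mechanism give none. If the laser does not affect pain, the drug rule removes equal shares and creates no false pain benefit. The common-threshold model is also close to a worst case, because every patient has paracetamol to hand.
- **The primary outcome.** A reader might infer that the rule discards usable angle data and so distorts the primary result by a known amount. The documents do not support this. There is no interim angle to discard, exclusion goes with removal of the apparatus, and the only figures above concern secondary pain outcomes.
- **Attendance.** A reader might count all 10 dates and obtain 18% and 40%. Day 0 is the day of allocation and cannot be missed after it. Patients are blinded by a sham, and nothing suggests that attendance differs by arm. These figures show lost numbers rather than bias.
- **Replacement.** Up to 3 extra patients per group offset the lost numbers. They do not stand in for the particular patients removed, so the comparison is still one of selected patients.
- **Other drugs may themselves shift pain and cytokine results.** This is a fair reason to want a restricted analysis, but as a sensitivity analysis: use of another drug may itself be a result of the treatment given.

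It could also be said that an unseen analysis plan may deal with this. That does not help here, because the article states the completer-only rule outright.

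**Conclusion.** The concern holds as a risk of bias that the article itself writes into the analysis. It is clearest for pain and analgesic use, where under the stated assumptions 22% to 44% of a true 0.5 SD benefit would be hidden (100% minus 78% to 56%). The direction is towards no effect, and the size depends on assumed rates of other drug use. For the primary angle outcome a link through complications is plausible, but no size can be given. The attendance rule alone could remove 17% to 37% of patients at assumed miss rates of 2% to 5% per date, at or beyond what the replacements cover. The textual facts are certain; the consequences are possible, not shown. The point should be settled before the data are analysed, because patients who are never followed up cannot be restored later.

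**What to change.** **Section 2.14.** Make the primary analysis set all randomised patients in the arm assigned, regardless of other drug use or missed visits. Use all VAS, analgesic and cytokine data already collected, with a mixed model for the repeated outcomes. Include the scheduled day-90 radiograph of every patient who has one, with its actual date. A mixed model cannot recover an angle that was never taken. Where there is none, report this by arm and reason and add a sensitivity analysis, for example multiple imputation and a worst-case range. Keep the completer analysis as a sensitivity analysis.

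**Section 2.4.** Separate stopping study treatment from exclusion from the analysis, and continue follow-up visits where the patient agrees. The clinical rule on apparatus removal is left as it stands.

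**Cost.** A rewritten analysis-set paragraph, a short missing-data paragraph, a clarified section 2.4, and some extra follow-up visits. If the package named in 2.14 does not fit mixed models, another has to be named. Other drugs and non-adherence may dilute or shift the pain and cytokine results, so the plan should state that it estimates the effect regardless of other drug use.

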## Discussion

3

The study was characterized as a randomized, double-blind, placebo-controlled trial to minimize measurement bias (also referred to as information, observation or measurement), which is the result of systematic differences in the way data about the event of interest is obtained from the various groups under study.^[50]^

Randomization should be performed in prospective studies comparing the effect of an intervention (prophylactic or therapeutic) with their respective controls. The researcher distributes the intervention at random through randomization; Thus, the experimental and control groups are formed by a random decision process.^[50]^

The term double-blind refers to those trials in which neither the patient nor those responsible for their care and evaluation know what treatment he is receiving. Blinding will be performed by randomization during delivery of envelopes, and the group to which the patient belongs is confidentially informed on the brown envelope. The main reason for introducing a placebo-controlled group is to make patients’ attitudes as similar as possible to those of the treated group.^[50]^

For our study, the calculated sample was based on the “amount of motion x time” variable, following the Kadam, 2010,^[41]^ sample size calculation formula: N = 2 (ZA - Z1-β) 2σ2 / Δ2 reaching a “n” of 34 patients (17 patients in each group), with 20% dropout, totaling 3 more individuals in each group. Research participant dropout is unlikely during treatment because it has the mini-implant installed. Therefore, we limited our study to a 90-day follow up.

Our approach was based on a problem that can be pointed as one of the most recurrent conditions in the population, which is the loss of the permanent lower first molar.^[51,52]^ Of various causes, this situation can result in mesial migration of the second molars,^[53,54]^ affecting even the anterior teeth, with opening of diastemas and midline deviations.^[53,55]^ In such cases it is still common to find infraosseous defects in the mesial of the inclined molar, accompanied by a gingival recession and a reduction of the interradicular space in the distal region.^[1]^

One solution to this problem would be the disinclination of this molar, a movement known as verticalization. This movement returns the parallelism to the teeth that may later receive a fixed or removable denture.^[56]^ Thus, vertical bone defects are eliminated or reduced without the need for surgical intervention, enabling adequate edentulous space to be obtained for prosthetic rehabilitation and improved crown-root ratio in periodontally compromised molars.^[56]^

For this verticalization there are several techniques described in the literature, such as removable appliances, fixed appliances associated with continuous arcs, mechanical segmented with cantilever springs.^[1,57,58]^ Basically, tooth movement mechanics can be performed through 2 types of system: 1 statically determined and 1 statically undetermined.^[59]^ In the first 1, an action arm (cantilever) is supported at 1 end of the fixed appliance, and the other is free, allowing better control of forces and predictability of side effects. In the second system, both ends of the wire are supported on the fixed apparatus, which generates unpredictability both in the direction and magnitude of the force.^[60]^

It is clear to say that for all these types of movement there is a need for the installation of fixed apparatus for force control. Being by itself a long treatment, we can still face deformations of the metal arches, observed mainly by inadequate forces on them during feeding, leading to increased treatment time, deleterious effects on dental elements located at the extremities of the prosthetic space and lack of control in orthodontic movement.^[61]^ Anchorage control has been the biggest challenge in orthodontics.^[61]^

In order to circumvent these adverse effects, Kamomi, 1997^[62]^ and Costa et al, 1998^[63]^ proposed the use of mini-implants as orthodontic skeletal anchorage. As advantages, they are small enough to be placed in any area of the alveolar bone, have rapid healing and can be easily removed after use.^[64]^ We also have that orthodontic forces can be applied immediately after implantation,^[64]^ resisting movement when subjected to the load of this orthodontic force.^[65]^ It is an interesting alternative because it does not require patient cooperation,^[66,67,68,69]^ being useful in reducing treatment time, not requiring the installation of a fixed apparatus, minimizing or eliminating any kind of unwanted effect on natural teeth that would previously receive these forces during standard orthodontic treatment.^[61]^

However, some care must still be taken. Working with excessive forces, there is a physiological decrease in the amount of tooth movement due to a decrease in vascularization in the compression areas, and an increase in bone density,^[12,13,70]^ besides being able to generate displacement of the mini-implant,^[3]^ its stability must be conferred to each consultation and the forces applied in a controlled manner (based on the use of tensiometer). Stability may also be compromised due to peri-implant tissue inflammation, generated by poor hygiene,^[71]^ which would warrant thorough oral hygiene guidance.

In the search for a safer and more controlled action of this movement, Photobiomodulation (PBM) also appears as an adjuvant method in the treatment. Pain (observed during tooth movement) may act decreasing prostaglandin^[72]^ and inhibit aracdonic acid production.^[24]^ The modulatory action in tissues is the result of the ability of PBM to accelerate metabolic changes, angiogenesis and increase in the repair process directly linked to bone formation.^[72–74]^ Increased bone resorption and neoformation are essential for orthodontic movement to occur.^[26]^

When working with PBM, the wavelength commonly used and with positive results is around 780 nm^[74,75]^ and 808 nm,^[40]^ that is, in the infrared range, which is the longest. penetration into human tissues.^[24]^ Of the few studies that sought to approach PBM during orthodontic movement, 2 had promising results: Fernandes, 2019,^[40]^ who worked with intrusion movement and wavelength 808 nm. Fernandes 2019^[40]^ had the laser application occurring monthly, always after the application of the forces. This frequency in Fernandes, 2019,^[40]^ can be explained by the fact that the elastomeric chains undergo degradation and loss of almost 76% of the amount of force after 21 days.^[76]^ In addition, numerous studies have shown that the ideal strength range for orthodontic movement ranges from 100 to 450 g.^[61]^ Petrey, 2010,^[77]^ stated that in implants up to 6 mm, the point of failure starts at 461gr of force. To ensure greater stability of the mini-implant in posterior mandibular region, forces less than 2N (200grs) applied immediately and a diameter larger than 1.0 mm are indicated.^[78]^

To analyze the effectiveness of a new method, pain and cytokine analysis are important markers. As subjective as it may be, pain can be measured by counting the number of analgesics consumed during the research^[47]^ and by applying the Visual Analog Scale (VAS), being a way to better interpret and understand the patient's pain, facilitating care planning and decision making, making care more humane and responsive to patient needs.^[46]^

Cytokines, on the other hand, are important inflammatory markers, and as proposed by Kinney, 2014,^[39]^ can be obtained from the manipulated site through crevicular gingival fluid (CGF), which can be easily collected with the help of delicate stems and which carries biological molecular markers collected from the inflamed periodontium.^[39]^

Finally, to analyze the tooth movement rate, tracings made on an initial and final panoramic radiography (after 3 months) will be performed following the model proposed by Ursi, 1990,^[45]^ to analyze dental angulation. It draws a mandibular line (which does not change because it is based on the bony base rather than the occlusal plane) and the long axis of the tooth^[45]^ forming an angle (the larger, the larger the inclination of the tooth). This is the simplest, fastest, most affordable method with the least radiation exposure to the patient.^[45,79]^
